### Screening measure

The Kessler-10 (K-10) is a well validated indicator of psychological distress [22] that will be used to screen individuals eligible to partake in the trial. The K-10 comprises of 10 questions about general wellbeing, experience of emotional states including symptoms of depression and anxiety over the past four weeks. Items are scored on a 5-point scale (range 0 to 50; higher scores indicate higher levels psychological distress), where a cut off of 20 [23] will be used to screen individuals with psychological distress in relation to COVID-19.

The Suicidal Ideation Attributes Scale (SIDAS) will be used to screen the presence of suicidal thoughts and their severity, and is also used as a secondary outcome. This scale consists of 5 items targeting varying attributes of suicidality including frequency, controllability, closeness to attempt, levels of distress associated with suicidal thoughts and consequent impacts on functioning. The SIDAS has demonstrated high internal consistency and good internal validity with GAD-7 and PHQ-9 [24].

### Primary outcome

The primary outcome will be severity of anxiety and depression symptoms as measured using the Hospital Anxiety and Depression Scales (HADS) [25]. The HADS is a 14-item scale consisting of two sub-scales: HADS-A (Anxiety, 7 items, range 0–21) and HADS-D (Depression, 7 items, range 0–21). Higher scores indicate more severe anxiety and/or depression. The minimal clinically important difference (as based on the effect size approach) has been determined at 1.32 for HADS-A and 1.40 for HADS-D and 1.17 for the HADS total score [26].

### Secondary outcomes

The presence of worry symptoms and generalised anxiety will be assessed using the Generalized Anxiety Disorder Scale (GAD-7) [27]. The GAD-7 has demonstrated good reliability, and validity [27] where higher scores indicate more severe symptoms (range 0–21). High levels of sensitivity (89%) and specificity (82%) relative to generalised anxiety disorder has previously been demonstrated using this scale [28]. Further, self-report and interviewer administered versions of this scale have demonstrated good comparability.

Symptoms of stress and anxiety related to COVID-19 pandemic will be assessed using the COVID Stress Scales (CSS) [29]. This scale was developed to index these concerns across 36 items comprising of five domains including 1) COVID danger and contamination fears, [2] COVID fears about economic consequences, [3] COVID xenophobia, [4] COVID compulsive checking and reassurance seeking, and [5] COVID traumatic stress symptoms. This scale had evidenced good reliability and internal consistency [29].

Positive psychological wellbeing will be assessed using the World Health Organization Well-Being Index (WHO-5) as a measure of responsiveness to group CWC or SC. The tool consists of 5 items on 6-point Likert scale, where respondents are asked to rate the extent to which each item related to them over the past 14 days. The WHO-5 has been used to detect aspects of depression in terms of positive mood, interest and energy [30].

All primary and secondary outcome measures have been detailed in Table 1.

**Table 1 Tab1:** Overview of measures administered at assessment time points

*Concept*	Pre-assessment T0	Post-treatment T1	2-months post-treatment (primary outcome timepoint) T2	6-months post treatment T3
1. Psychological distress	K-10 (**screener**)			
2. Anxiety and depression	HADS (**primary outcome)**	HADS	HADS	HADS
3. Generalised anxiety	GAD-7	GAD-7	GAD-7	GAD-7
4. Wellbeing	WHO-5	WHO-5	WHO-5	WHO-5
5. COVID stress	CSS	CSS	CSS	CSS
6. Suicidal Ideation	SIDAS	SIDAS	SIDAS	SIDAS

### Facilitator selection, training, and supervision

The CWC and SC interventions will be conducted by trained peer facilitators, who will be male and female non-specialist providers recruited from CHRIST (Deemed to be University) campuses across India. They will receive 8 days of training in basic counselling skills, delivery of CWC and SC techniques, group facilitation and self-care. At the end of training, all facilitators will be required to conduct a practise group of both CWC and SC interventions under the close supervision of trained clinical psychologists. In the event that a practice cycle cannot be conducted, a role-play competency assessment will be conducted. To this end, both practice cycles and role-plays will be used to assess facilitator competency prior to implementation of groups for the RCT. Regular weekly supervision will be provided remotely by video teleconferencing with a clinical psychologist (DK, KD, SA, or SY) to ensure treatment adherence and provide ongoing support to facilitators.

CWC and SC groups will be conducted across two cycles from Oct 2021 to Dec 2022 such that training, practice cycles and groups sessions can be run outside of assessment and holiday periods as determined within the CHRIST (Deemed to be university) college semester schedules. Group debrief and feedback sessions will be conducted mid-way and at the end of cycle 1 implementation of sessions such that important learnings can be carried forward to cycle 2 of the RCT.

### Fidelity and blinding

Adherence to the adapted CWC and SC protocol will be ensured by weekly group supervisions including the group facilitators and supervisors. To evaluate treatment fidelity, a sample of 10% of the CWC and SC sessions will be independently rated for adherence. A structured observation form comprising of the presence of the elements pertaining to both CWC and SC programs will be scored by trained members of the research team. Sessions will not be transcribed but raters will make ratings on the basis of audio files that can be accessed by encrypted passwords. To ease the burden of rating of many treatment sessions, different raters will be recruited throughout the course of the trial. Raters will be blind to treatment condition of the sessions they rate, and will be required to nominate what therapy components were present in each session and the quality with which these components were administered.

### Data management and trial monitoring

A trial management committee of the principal investigator, co-investigators, and local research coordinators will monitor the implementation of study procedures on an ongoing basis. Any adverse events that occur during the trial (e.g., increase in distress, suicidal attempts) in a participant that is not related to the CWC intervention, will be recorded by the research team and reported to the study’s trial management committee and Trial Sponsor. These adverse reactions will be referred to appropriate services either within the university counselling service and/or through external psychological support. These services will be nominated by the local clinical psychologist (ET), external to the study, but within the university.

Given the nature of this intervention trial, participants will be required to have their identities known to the implementation staff in order to be contacted for any adverse events and related ongoing care, post and follow-up assessments. All assessment data will be collected from online surveys (administered via the Kobo data collection software) and will be imported into the SPSS statistical analysis database for data management and analysis. Access to assessment data will be restricted to the research assistant team who will be blind to intervention allocation throughout the trial. Further details of data security and storage can be found in ethical protocols, which are available on request. Audio recordings of group sessions will be collected in line with CONSORT requirements for subsequent supervision and assessment of treatment fidelity. The research implementation staff will have access to the data via the UNSW Research Long Term Data Store Interface.

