Despite the success of scalable interventions, an outstanding question is clarification of the extent to which treatment gains are attributable to the strategies taught in the programs or to non-specific treatment effects such as counsellor attention or group involvement. All trials of PM + have compared the intervention with usual care, and in doing so have not disentangled these elements. To address this gap, the current study will assess the effectiveness of CWC delivered by lay peer facilitators to target distress resulting from the COVID-19 pandemic in a young adult population and compare this to non-directive group counselling. In using a non-specialist supportive framework involving peers to deliver this evidence-based program, we aim to address potential gaps in access to care, insofar as stigma may act as a barrier in young people utilising evidence-based care. A secondary aim of this study is to assess potential therapeutic impacts of attention and support afforded by peers in driving the effectiveness of CWC. We predict that CWC would lead to greater reductions in common mental health problems including worry, anxiety, depression, and suicidality relative to supportive counselling.

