## Methods

### Aims & hypotheses

This study will assess the effectiveness of an adapted version of CWC to specifically target mental distress arising from the COVID pandemic in a cohort of university students in India. The randomized controlled trial (RCT) will compare CWC with Supportive Counselling (SC) in participants reporting moderate to severe psychological distress in a group format. The primary hypothesis is that those receiving group CWC will report lower psychological distress compared to those who received supportive counselling. To this end, we hypothesize that the impact of social support and alliance afforded by the supportive counselling condition will not exceed the therapeutic effects of evidence-based skills covered in CWC. The primary outcome measures are anxiety and depression, as measured by the Hospital Anxiety and Depression Scale (HADS, [21] subscales.

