### Randomization

The randomization will be conducted by a computerized software on a 1:1 basis and will occur following completion of the T0 assessment. Two project managers who are independent of any other aspects of the treatment study being conducted in Bangalore, India will allocate individuals to CWC or SC groups. Following this time, individuals will be invited for the introductory online session with the group facilitator.

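### As worded, the only adverse-event rule gives CWC-related events no recording or reporting route, and it conflicts with its own sentence and the next

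*Protocol article*

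**What the plan says.** The rule stands in the Protocol article, Methods, Data management and trial monitoring. Its sentence opens broadly: "Any adverse events that occur during the trial (e.g., increase in distress, suicidal attempts"). It then narrows. The event is one "in a participant that is not related to the CWC intervention, will be recorded by the research team and reported", and the recipients are given in "reported to the study’s trial management committee and Trial Sponsor". The next sentence begins "These adverse reactions will be referred to appropriate services".

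The following paragraph of the same section mentions adverse events once more. Participants must be identifiable to staff "in order to be contacted for any adverse events and related ongoing care, post and follow-up assessments". That concerns contact and care and sets no duty to record or report.

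Three other places bear on the point:
- Aims & hypotheses names the comparator: "The randomized controlled trial (RCT) will compare CWC with Supportive Counselling (SC"). No relatedness condition is stated for SC.
- Table 1 schedules HADS, GAD-7 and SIDAS at all four assessments, T0 to T3, without distinction by arm.
- Statistical analysis lists HADS, GAD-7, CSS, SIDAS and WHO-5. It names no adverse-event test, count or table.

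**The concern.** A safety record exists above all to hold events that the intervention may have caused. Here the condition attached to recording and reporting is that the event is unrelated to CWC. Followed to the letter, staff would have an instruction for unrelated events and none for related ones, and the committee and sponsor might not receive the events that say most about CWC.

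The condition also works unequally. It names CWC alone. An SC participant does not receive CWC, so any event in that arm meets the condition. A CWC participant's event meets it only after someone has judged it unrelated, and that judgement cannot be made without knowing the arm. Any count built from such a record would lean towards CWC.

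The sample makes this more than a formality. Participants are enrolled because they screen positive for distress, the facilitators are non-specialist peers, and suicide attempts are one of the rule's own examples. An event that is not written down at the time may not be recoverable later.

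**Working it through.** **Step 1: does any reading of the rule cover CWC-related events?** The phrase about not being related could attach to the event or, grammatically, to the participant. On the first reading, events related to CWC are left out. On the second, participants connected with CWC are left out. Either way, CWC-related harm is outside what the sentence says will be recorded and reported.

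**Step 2: does another part of the document supply the missing route?** The only other mention, on identifiability, covers contact and care. Statistical analysis adds none. So the document states no route.

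**Step 3: does the wording agree with itself?**
- The sentence begins with adverse events of any kind and then excludes a class of them.
- The next sentence calls the captured events reactions. That word usually implies a causal link, yet these events have just been defined as unrelated to CWC.

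The wording does not agree with itself, and the passages must be reconciled.

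**Step 4: how large could the distortion of a later table be?** The document gives no adverse-event rate and no share of events expected to be judged related, so there is no stated figure to reproduce. What follows is an illustration under assumed values.

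Let r be the true event risk in the SC arm, RR × r the true risk in the CWC arm, and s the share of CWC-arm events judged related and therefore not recorded. In the SC arm that share is 0.

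- Recorded risk, SC: r
- Recorded risk, CWC: RR × r × (1 - s)
- Recorded risk ratio: RR × (1 - s)

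r cancels, so the ratio needs no assumed event rate. Allocation is 1:1, but the ratio of risks would be the same under any allocation.

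| True RR | s = 0 | s = 25% | s = 50% | s = 100% |
|---|---|---|---|---|
| 1.0 | 1.00 | 0.75 | 0.50 | 0 |
| 1.5 | 1.50 | 1.125 | 0.75 | 0 |
| 2.0 | 2.00 | 1.50 | 1.00 | 0 |

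For every s above 0 the recorded ratio is lower than the true one, which favours CWC.

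**Step 5: a special case.** Suppose CWC raises risk (RR above 1) and exactly the excess events are judged related. Then s = (RR - 1)/RR, and the recorded ratio is RR × (1 - (RR - 1)/RR) = RR × (1/RR) = 1.0. For RR = 2.0, s = 1/2; for RR = 1.5, s = 1/3. Correct attribution would then remove the excess from the record altogether.

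**Step 6: after the fix.** If every event is recorded whatever its relatedness, s = 0 and the recorded ratio equals the true one.

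**The case against.** Several points on the other side have force.

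- **The word only is not in the text.** The article says that unrelated events will be recorded; it does not say that related ones will not be. A journal article condenses, and a fuller procedure may exist elsewhere. This stands as a caution about what was intended or done. It does not repair the published sentence, which states a rule with a wrong boundary and is not merely short on detail.
- **A drafting slip is likely.** The broad opening, the term in the next sentence, the unfiltered mention of contact for adverse events and the awkward grammar all point that way. A reader might infer that the trial deliberately keeps CWC-related harm off the record. The document does not support that. The slip still matters, because the sentence governs safety capture and staff could follow it as printed.
- **No safety comparison is planned in this document.** A reader might infer that a specified between-arm safety analysis is biased. Statistical analysis names none, so the distortion in the working applies only to a table or count that someone later builds from the recorded events.
- **Part of the harm signal is measured independently.** SIDAS, HADS and GAD-7 are collected in both arms at every assessment, so worsening distress and suicidal ideation stay visible by arm. This stands, and it narrows the exposure. Scheduled questionnaires do not replace a record of discrete events such as suicide attempts.
- **The size is hypothetical.** No value of s can be drawn from the document; at s = 50%, a halving simply restates the assumption. The direction is what the wording fixes, not the amount.

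**Conclusion.** The point holds in a limited form. The one adverse-event recording and reporting rule in the document, read literally, gives events related to CWC no stated route to the trial management committee and sponsor, while every SC event qualifies. It also conflicts with the opening of its own sentence and with the term used in the next.

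The exposure is to discrete events and to any later tabulation of recorded events. No efficacy estimate and no stated analysis is affected.

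The size in the working rests on four assumptions: the sentence is followed as printed; no SC event is judged related to CWC; events come to notice equally in both arms; and s takes the values shown, none of which comes from the document. If a slip is confirmed and all events are in fact recorded, s is 0 and only the wording needs correcting.

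**What to change.** - Reword the sentence so that every adverse event in either arm is recorded and reported to the trial management committee and sponsor, whatever its judged relatedness.
- Record relatedness, to CWC or to SC, afterwards as a data field, so that it describes events and does not select them.
- Tabulate any reported adverse events by randomised arm.
- In the next sentence, replace the word reactions with events so that the passage agrees with itself. This is a change of term; which events the referral arrangement is meant to cover is for the sponsor to confirm.
- If events have already been logged, state which rule was applied in practice.

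The cost is a short amendment to the wording and one field on the event form. It needs no extra staff, visits or procedures.

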### Sample size

The sample size calculation for this treatment trial was based on a two-group comparison of the primary outcome at the 2-month follow-up timepoint. In order to obtain estimates of parameters, a comparable data set from a recent treatment trial in a high-income setting was used [20]. The power analysis indicated that to achieve a moderate effect size of (0.6) a sample size of 90 participants would be needed per arm to provide power of 0.95 (alpha = 0.05, two-sided); on the expectation that there would be approximately 10% attrition at the 2-month follow-up assessment, it was estimated that a total of 200 participants would need to be enrolled into the study.

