## Discussion

This study will evaluate CWC in managing COVID-19 related distress in the sequalae of the COVID-19 pandemic. The trial outlined in this protocol is the first to assess the effectiveness of the CWC program relative to an active control intervention, and in a LMIC setting with young adults in a college-going population. The extent to which the effectiveness of CWC relative to SC is demonstrated, this trial will shed important insights on the active components of this transdiagnostic intervention.

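### The stated effect (0.6), power (0.95) and 90 per arm do not agree (the inputs give 74 per arm), and the document does not support 0.6 against Supportive Counselling

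*Protocol article*

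**What the plan says.** The Sample size section of the protocol article sets out a complete calculation. It is "based on a two-group comparison of the primary outcome at the 2-month follow-up timepoint". The target is "to achieve a moderate effect size of (0.6" on the standardised scale, the test is at "alpha = 0.05, two-sided", and the result is that "a sample size of 90 participants would be needed per arm to provide power of 0.95". An expected 10% loss by 2 months then raises the total to 200. The Randomization section gives 1:1 allocation. No allowance for clustering or for more than one primary test is mentioned.

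On the source of the planning values, the same section says that "a comparable data set from a recent treatment trial in a high-income setting was used". The Background identifies the cited study as the earlier videoconference trial of CWC, an adaptation of Problem Management Plus (PM+). The Background also says: "All trials of PM + have compared the intervention with usual care". The Discussion says that the present trial "is the first to assess the effectiveness of the CWC program relative to an active control intervention". Under Interventions, SC has the same number and length of weekly video sessions as CWC and is also led by a trained peer.

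**The concern.** There are two separate points.

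1. The effect size, power, alpha and sample size are tied together: any three fix the fourth. The four printed here do not fit, so at least one is wrong or an input has been left out. A reader cannot tell which, and cannot tell what difference the trial was sized to detect.

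2. The source data set is called comparable, but elsewhere the article describes it in terms that imply no active control. A contrast with usual care includes the effect of attention and group contact. SC supplies those to the control arm here. An effect size that is reasonable against usual care may therefore be too large against SC, and the 95% figure applies only if 0.6 is realistic for the contrast being tested.

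**Working it through.** **Inputs.** d = 0.6, power 0.95, two-sided alpha 0.05, 90 per arm and 10% attrition (all from Sample size); 1:1 allocation (Randomization); groups of 4 to 5 (Interventions).

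**Step 1: the stated n.** Normal approximation: n per arm = 2(z₀.₉₇₅ + z₀.₉₅)² / d² = 2(1.960 + 1.645)² / 0.36 = 72.2, so 73. The noncentral-t calculation gives 73.2, so 74. The stated figure is 90. The gap is 90 − 74 = 16 per arm, or 16/74 = 22%, which is more than rounding.

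**Step 2: attrition.** 90/0.9 = 100 per arm, 200 in total. This step reproduces, and it shows that attrition is added after the 90 and so cannot explain it. Starting from 74: 74/0.9 = 82.2, so 83 per arm and 166 in total.

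**Step 3: what 90 per arm delivers.** Power at 0.6: Φ(0.6 × √(90/2) − 1.960) = Φ(4.025 − 1.960) = 0.981; by noncentral t, 0.979. Detectable effect by noncentral t: d = 0.54 for 95% power and d = 0.42 for 80%.

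**Step 4: could an unstated input explain 90?**

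| Variant | n per arm |
|---|---|
| One-sided alpha 0.05 | 61 |
| Alpha halved to 0.025 (two HADS subscales) | 84–86 |
| Rank test (efficiency 0.955) | 78 |
| 10% dropout already inside the 90 | 81–83 |
| Design effect 1 + (5 − 1) × 0.05 = 1.20 (assumed ICC 0.05, groups of 5) | 88–89 |
| Design effect, assumed ICC 0.01–0.10, groups of 4–5 | 76–104 |

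Only a design effect comes close, and none is stated.

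**Step 5: smaller effects.** Two-sample t-test with 90 analysed per arm. The clustered column replaces 90 by 90 / [1 + (m − 1) × ICC], with an assumed ICC of 0.01 to 0.10 and m = 4 to 5, so an effective 87.4 down to 64.3 per arm. The effects below 0.6 are assumptions; the document gives no figure for CWC against an active control.

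| d | Power, no clustering | Power, clustered |
|---|---|---|
| 0.6 | 98% | 92–98% |
| 0.5 | 92% | 80–91% |
| 0.4 | 76% | 61–75% |
| 0.3 | 52% | 39–50% |

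**Step 6: the source of the parameters.** The Background makes the cited study a trial of adapted PM+. It also says that PM+ trials used usual care as the comparator. The Discussion places the first active-control comparison of CWC in the present trial. The three statements together point to a source without an active control.

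**The case against.** The strongest reply is that the error is on the safe side. At d = 0.6, 90 analysed per arm gives 98% power, so the 95% claim is met. If the Abstract's 90 per arm are those randomised and 10% are lost, 81 remain and power is still 97%. With an assumed ICC of 0.05 and groups of 4.5, it is about 96%. This stands. A reader might infer from the mismatch that the trial is too small for its stated effect, and the figures do not support that. Only at the top of the assumed ICC range (0.10) does power at 0.6 fall slightly below 95%, to 92–94%.

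A reader might also infer that 0.6 is the effect seen in the earlier trial. The text says only that its data set was used to estimate parameters. Those could be the standard deviation or the attrition, and 0.6 could be a chosen target. Nor can it be said that the power statement concerns some other contrast: it is framed as the two-group comparison at 2 months, which is CWC versus SC.

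The absence of an active control in the source is inferred from three statements and is not stated outright. The Discussion's claim to be first is also joined to the setting and population. The inference is likely but not certain.

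A condensed article may leave the justification of an effect size to the full protocol, so its absence alone is no finding. What stands is that the article calls the source comparable and elsewhere describes it as differing on the feature this trial was built to test.

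Finally, a reader might infer that a non-significant result is meant to show that CWC content adds nothing. The document does not say how such a result would be read, so that charge is not made here.

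**Conclusion.** The arithmetic point is firm. The printed inputs need 74 per arm, not 90, and 90 analysed per arm corresponds to about 98% power at 0.6, or 95% at d = 0.54. It rests on a plain two-sample comparison, which is what the section describes. It is a statement to correct and does not weaken the trial at 0.6.

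The second point is more limited. As written, the document does not support 0.6 for CWC versus SC, because the parameter source apparently had no active control. If the true difference is smaller, power is well below the headline: 76% at an assumed 0.4 and 52% at an assumed 0.3, both before clustering. Whether the true effect is smaller cannot be settled from the document.

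**What to change.** Keep the planned enrolment and change the Sample size text:

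- Either state the input that takes 74 to 90 (for example the design effect, with its ICC and group size), or restate the result as 90 analysable per arm, giving 95% power for d = 0.54 or 80% for d = 0.42 before clustering.
- Say whether 0.6 was the earlier trial's effect or a chosen target, and that the source data set had no active comparator, if that is so.
- Report power for d = 0.3 to 0.5 against SC beside the headline figure, with and without clustering, and with the assumed ICC shown.

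The cost is a few restated figures and sentences, with no extra participants. The only downside is that the power statement looks less favourable for smaller effects.
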